### Aims

The primary aim of this pilot RCT is to establish the acceptability of the WTW intervention to service users by evaluating if participants can be recruited into the study and if they complete the intervention. Secondary aims are to estimate if, compared with treatment as usual (TAU), the WTW intervention (1) reduces sedentary behaviour (reduce the total minutes per day of sedentary behaviour) and (2) increases daily physical activity (light, moderate and vigorous in minutes per day) in people with SMI. In addition, we will consider the impact of the WTW versus TAU on glucose regulation, progression to T2DM and MetS risk factors, including BMI and waist circumference.

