### Participants

Participants will be recruited from among community teams in SLaM. The following eligibility criteria will be used:Diagnosis of any SMI (schizophrenia, psychosis, bipolar disorder and major depression)Meeting any one of the following criteria as determined by a care co-ordinator:OverweightAt risk for or have T2DMIn the clinician’s view, have a sedentary lifestyleSmoke tobacco
Ability to provide informed consentAbility to understand English

We aim to recruit 40 participants, 20 in the intervention group and 20 in the control group. This number is based on recruiting a big-enough sample to assess the feasibility of the study and on the resources available [22].

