#### Secondary outcomes

Sedentary behaviour and physical activity time per day will be recorded. All participants will be required to wear a wrist-worn GENEActiv accelerometer (GENEActiv, Kimbolton, UK) for at least 4 days (including 1 weekend day if possible) at baseline that will measure habitual sedentary behaviour and walking activity each day. The accelerometer will record how many minutes per day each participant is sedentary and engages in light, moderate and vigorous physical activities. A recording is made of each 60-second period (called an ‘epoch’), and this is classified as being either sedentary or light, moderate or vigorous physical activity. The cut-off points were defined according to metabolic equivalents (METs) of sedentary (<1.5 METs), light (1.5–3.99 METs), moderate (4.00–6.99 METs) and vigorous (>7+ METs), based on standardised algorithms with high sensitivity and specificity with oxygen consumption [23]. For this study, we are interested in the total minutes of sedentary behaviour per day, number of disruptions in sedentary behaviour and total time spent in physical activity (minutes per day in light, moderate and vigorous activity). Specifically, we are interested in the change in average minutes of sedentary behaviour and physical activity before and after the WTW intervention. We will measure if the WTW intervention group changes pre- and post-intervention in sedentary behaviour and physical activity and also measure if this differs from the control group. The following outcomes will also be measured at both baseline and follow-up:
*Anthropometric measures*: We will measure BMI according to the IDF criteria [24], including height, weight and waist circumference.
*Self-report sedentary behaviour and physical activity*: The International Physical Activity Questionnaire (IPAQ) [25] will be used to capture self-reported physical activity and sedentary behaviour. The IPAQ has questions asking about the amount of vigorous and moderate activity done in the last 7 days, how often the person has walked for more than 10 minutes in the last 7 days, and how many hours the person is sedentary on a usual day.
*Motivation to engage in physical activity*: The Behavioural Regulation in Exercise Questionnaire-2 (BREQ-2) [26] is a 19-item interviewer-administered questionnaire designed to consider an individual’s motivation towards exercise. The BREQ-2 has been validated in people with schizophrenia [27].

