### Randomisation

The randomisation will be done by a researcher independent of the study using the random sequence generator in random.org. The researchers will not know which arm the participant has been consigned to before the baseline assessment. Participants will be told if they have been randomised to either the intervention and control group after the baseline assessment.

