### Analysis

For the primary aim and to evaluate feasibility, we will calculate the percentage of people approached who participate in the intervention and the percentage who complete the intervention. We will use the process evaluation to understand how the intervention was experienced by participants and any changes that they think would improve the intervention.

To evaluate the effectiveness of the intervention, we will investigate changes in pre- and post-test scores for the secondary outcome measure (total minutes of sedentary behaviour per day and total minutes of physical activity) of the WTW participants. We will also investigate changes in the pre- and post-test scores for the other outcome measures. We will compare the mean changes in sedentary behaviour and physical activity (light, moderate and vigorous) in the WTW group versus the control group.

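### The between-arm comparison of mean changes names no baseline adjustment, which at 20 per arm costs precision and leaves the estimate sensitive to chance baseline imbalance

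*Protocol article*

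**What the plan says.** The Analysis section gives the between-arm method for sedentary behaviour and physical activity in one sentence: "We will compare the mean changes in sedentary behaviour and physical activity (light, moderate and vigorous) in the WTW group versus the control group". The Secondary outcomes section frames the target the same way: "we are interested in the change in average minutes of sedentary behaviour and physical activity before and after the WTW intervention". It continues: "We will measure if the WTW intervention group changes pre- and post-intervention in sedentary behaviour and physical activity and also measure if this differs from". Here the comparator is the control arm. Neither section mentions the baseline value as a covariate.

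The baseline value is available. Participants wear the accelerometer "for at least 4 days (including 1 weekend day if possible) at baseline that will measure habitual sedentary behaviour", and the Follow-up assessment section repeats all measures except the sociodemographic ones at the end of the 17-week programme.

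The sample is small: "We aim to recruit 40 participants, 20 in the intervention group and 20 in the control group". On allocation, the Randomisation section says: "The randomisation will be done by a researcher independent of the study using the random sequence generator in random.org"; it states no stratification or minimisation. The Aims section places these outcomes second: "Secondary aims are to estimate if, compared with treatment as usual (TAU), the WTW intervention" reduces sedentary time and increases activity. The primary aim is acceptability, judged by recruitment and completion.

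**The concern.** A difference in mean change fixes the coefficient on baseline at 1. A baseline of about four days of wear is a noisy measure of habitual behaviour, and the follow-up comes about 17 weeks later, so the regression slope of follow-up on baseline is likely to be below 1. Two things follow.

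- **Precision.** Subtracting the whole baseline adds its noise to the outcome. A model that estimates the slope removes only as much of the baseline as predicts follow-up.
- **Sensitivity to imbalance.** If one arm starts more sedentary by chance, regression to the mean makes it appear to improve more. This flatters WTW if WTW starts more sedentary, and counts against it if the control arm does. For activity minutes the arm that starts less active is the one credited.

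At stake is how usable the estimated effects on sedentary behaviour and activity are. Those effects are the stated secondary aims, and 40 people leave little precision to spare.

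**Working it through.** The plan gives no power, SD, effect size or correlation, so it has no figure to reproduce. Its sample size rests on other grounds: "This number is based on recruiting a big-enough sample to assess the feasibility of the study and on the resources available". The check therefore compares two estimators at the planned size.

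**Inputs.** From the protocol article: n = 20 per arm, N = 40 (Participants). Assumed: equal SD (s) at baseline and follow-up, complete follow-up, and a baseline to follow-up correlation r shown over a range. All results are in units of the outcome SD.

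**Step 1: chance imbalance.** The SD of the standardised baseline difference is sqrt(1/20 + 1/20) = sqrt(2/20) = 0.316. Under a normal approximation, the probability of a difference above 0.3 SD in either direction is 34%, and above 0.5 SD it is 11%.

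**Step 2: precision.** The variance factors per arm, in units of s², are:

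- change score: 2(1 − r)
- baseline-adjusted: (1 − r²) × (N − 3)/(N − 4) = (1 − r²) × 37/36, where 37/36 is the small-sample cost of estimating the slope

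The standard error is sqrt(factor × 2/20). For r = 0.5 the change score gives 2 × 0.5 = 1.000 and SE = sqrt(0.1000) = 0.316. Adjustment gives 0.75 × 37/36 = 0.771 and SE = sqrt(0.0771) = 0.278. The variance ratio is 0.771, and 40/0.771 = 52.

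**Step 3: shift for a given imbalance.** If the baseline difference is d, the change-score estimate is displaced by −(1 − r) × d. For d = 0.316 and r = 0.5 that is −0.5 × 0.316 = −0.158.

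| Assumed r | SE, change | SE, adjusted | Variance ratio | People needed by change score to match 40 adjusted | Shift at 0.316 SD imbalance |
|---|---|---|---|---|---|
| 0.3 | 0.374 | 0.306 | 0.67 | 60 | 0.22 |
| 0.5 | 0.316 | 0.278 | 0.77 | 52 | 0.16 |
| 0.7 | 0.245 | 0.229 | 0.87 | 46 | 0.09 |
| 0.9 | 0.141 | 0.140 | 0.98 | 41 | 0.03 |
| 0.95 | 0.100 | 0.100 | 1.00 | 40 | 0.02 |

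Comparing follow-up values alone has SE sqrt(2/20) = 0.316 whatever r is. So at r = 0.5 the change score does no better than ignoring baseline, and below 0.5 it does worse.

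**Step 4: simulation check.** For each of r = 0.3, 0.5, 0.7 and 0.9, 40,000 trials of 20 per arm were simulated with no treatment effect. Over all randomisations both estimators averaged within 0.002 of zero. The simulated variance ratios were 0.665, 0.766, 0.870 and 0.975. Among trials with a baseline difference of 0.25 to 0.40 SD, the change score averaged −0.227, −0.158, −0.097 and −0.034, and the adjusted estimate stayed within 0.002 of zero.

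**The case against.** The strongest reply is that the sentence in the Analysis section names no test or model and does not say that the comparison is unadjusted. A regression of change on arm and baseline is also a comparison of mean changes, and an analysis plan that is not shown may specify it. This stands in part: the document does not rule adjustment out. But it does state a between-arm method, in two places, and neither mentions baseline. The plain reading is the unadjusted one, and the point concerns that stated method rather than detail left to another document.

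The second reply is that the size depends on a correlation found nowhere in the document. That is correct, and at r = 0.9 or above little or nothing is gained. Four days of wear repeated some 17 weeks later makes so high a value unlikely, but this is a judgement, not a documented figure.

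A reader might also infer stronger claims that the document does not support:

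- **That the planned analysis is biased outright.** It is not. Under randomisation the change score is unbiased on average, and the bias is conditional on the observed imbalance.
- **That the error favours WTW.** It can go either way.
- **That a flawed effect or SD estimate would size the next trial.** The Discussion makes the larger trial depend on acceptability, and no passage says that it will be sized from these estimates. The SD and the correlation can in any case be computed from the same data whichever estimator is reported.
- **That the main conclusion of the pilot is at risk.** Recruitment and completion percentages do not use this comparison.

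**Conclusion.** The point holds as a modest, worthwhile correction to the analysis of secondary outcomes. As written, the comparison of mean changes is less precise than a baseline-adjusted one over most plausible correlations: about 33%, 23%, 13% and 2% of the variance could be saved at r = 0.3, 0.5, 0.7 and 0.9, and nothing near 0.95. An imbalance of the size expected by chance (0.32 SD) would move the result by about 0.22, 0.16, 0.09 or 0.03 SD at those correlations. These figures assume equal SDs at the two time points, 20 per arm with full follow-up, and a correlation that the document does not give.

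**What to change.** In the Analysis section, replace the sentence on the between-arm comparison with wording such as: *Sedentary minutes and light, moderate and vigorous activity minutes per day will each be compared between arms by linear regression of the follow-up value on allocated arm and the baseline value of the same outcome, reporting the adjusted mean difference with its 95% CI. Mean changes in each arm will be reported descriptively.* Using the change as the dependent variable in the same model gives an identical arm effect, so the change framing in the Secondary outcomes section can stay. If an analysis plan already adjusts for baseline, the sentence should be brought into line with it.

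The cost is one degree of freedom per model (residual degrees of freedom fall from 38 to 37 with 40 people). No new data are needed, and although the Trial status section says recruitment has ended, nothing in the conduct of the trial would change.

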## Discussion

This pilot aims to evaluate the feasibility and acceptability of an intervention to support people with SMI using secondary mental health services to increase their level of activity. If WTW proves to be acceptable, we plan to undertake a larger RCT to assess the effectiveness of such an intervention.

The physical health of people with SMI has become a priority for both primary and secondary services in recent years to address the identified mortality gap. Improving the physical health of people with SMI will require a multifaceted approach that includes the identification of physical health risks to ensure effective treatment is given and interventions are initiated to reduce physical health risks. This is happening at a time when there is a growing awareness of the risks of sedentary behaviour in the general population which is leading to approaches to reduce sedentary behaviour in all.

National Institute for Health and Care Excellence guidelines for people with schizophrenia recommend that interventions be offered to support people with SMI to be more active [34], but there are few evidence-based interventions which clinicians can offer. An intervention that is found to be acceptable to people with SMI would be a welcome addition to the field.

## Trial status

The trial is ongoing and no longer recruiting.

## Abbreviations

BMI: Body mass index
BREQ-2: Behavioural Regulation in Exercise Questionnaire-2
CRP: C-reactive protein
CVD: Cardiovascular disease
IDF: International Diabetes Federation
IPAQ: International Physical Activity Questionnaire
MDD: Major depressive disorder
MET: Metabolic equivalent
MetS: Metabolic syndrome
PHE: Public Health England
RCT: Randomised controlled trial
SLaM: South London and Maudsley NHS Foundation Trust
SMI: Serious mental illness
T2DM: Type 2 diabetes mellitus
TAU: Treatment as usual
TUG: Timed Up and Go Test
WALC-S: Walk, Address sensations, Learn about exercise, Cue exercise behaviour for persons with schizophrenia spectrum disorders programme
WEMWBS: Warwick-Edinburgh Mental Wellbeing Scale
WHO: World Health Organisation
WTW: Walk This Way study
